### Economic analysis

2.7

The cost of DOACs will be compared with that of VKAs, following the methodological guidelines for this type of study proposed by the International Society for Pharmacoeconomics and Outcomes Research (ISPOR)^[36]^ and the International Network of Agencies for Health Technology Assessment (INAHTA).^[37]^

After comparing the average cost of both groups of drugs and estimating their confidence intervals, a regression model will be developed to determine which factors may have the most substantial influence on determining costs. A generalized linear model (GLM) will be derived, which, given the asymmetry of the cost variable, will be based on the gamma family of distributions, with a log link function,^[38]^ because these give a best fit to the data when estimating the impact of the factors associated with the composition of patient costs.

### Sensitivity analysis

2.8

A univariate (1-way) deterministic sensitivity analysis will be carried out, in the items which the greatest impact on the composition of the cost, or in which there may be a uncertainty with the real price.^[39]^ This will allow us to test the robustness of our results.

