**Methods::**

Population-based cohort study, in which the cost of the 2 treatment groups will be evaluated. Direct costs (pharmacy, primary care, emergency and hospitalization) and indirect costs (lost productivity) will be included from a social perspective. Effectiveness (assessed as the occurrence of a health event, the 1 of primary interest being stroke) will be determined, with a 2-year time horizon and a 3% discount rate. The average cost of the 2 groups of drugs will be compared using a regression model to determine the factors with the greatest influence on determining costs. We will carry out a univariate (‘one-way’) deterministic sensitivity analysis.

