### Measurement of effectiveness

2.6

The primary health event in this project will be “ischaemic stroke” and the indicator of cost-effectiveness will be “avoided strokes”. To estimate avoided strokes we will determine the total economic cost for the 2 pharmacological groups, as well as the number of strokes registered during the 2 years of the study period. Finally, we will compare the groups and thereby determine the economic cost of avoiding a stroke.

Secondarily, we will determine the appearance of the following health events during the 2 years of the study:

Ischaemic events:(1)Ischemic stroke.(2)Other thromboembolic events (transient ischaemic attack (TIA), angina, acute myocardial infarction, and peripheral embolism).•Haemorrhagic events:(1)Intracranial haemorrhage.(2)Gastrointestinal bleeding.(3)Other haemorrhages.•All-cause mortality.

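### The one-way variation of cost items in section 2.8 cannot test the robustness of the cost per stroke avoided, because no described step carries sampling error in strokes avoided into the ratio

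*Protocol article*

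**What the plan says.** Section 2.6 (Measurement of effectiveness) builds the primary result from the total cost in each drug group and "the number of strokes registered during the 2 years of the study period". The groups are then compared to "thereby determine the economic cost of avoiding a stroke". The result is therefore a cost difference divided by a difference in strokes.

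Section 2.7 (Economic analysis) plans one form of statistical uncertainty: "After comparing the average cost of both groups of drugs and estimating their confidence intervals". A gamma model with log link follows, chosen "given the asymmetry of the cost variable", to find the factors that drive cost.

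Section 2.8 (Sensitivity analysis) states "A univariate (1-way) deterministic sensitivity analysis will be carried out", applied "in the items which the greatest impact on the composition of the cost" or where the true price is uncertain. It then says "This will allow us to test the robustness of our results". The abstract names the same single analysis: "We will carry out a univariate (‘one-way’) deterministic sensitivity analysis".

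No interval is described for strokes avoided or for the ratio.

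**The concern.** A one-way deterministic analysis changes one input at a time and recomputes the answer. Every input named in section 2.8 is a cost item or a price, so each variation moves the numerator and leaves the count of strokes avoided exactly as observed. Such an analysis cannot show how the ratio would differ in another sample of patients.

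That matters here for three reasons.

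- The denominator is a difference between two small risks, and a ratio becomes unstable as its denominator approaches zero. Section 4.1 (Limitations) itself warns that two years may be too short for events to appear.
- Cost and stroke are linked. Section 2.5 counts hospital costs, so a stroke admission enters both parts of the ratio. A chance shortfall of strokes in the DOAC group raises strokes avoided and lowers incremental cost together. Separate intervals for mean costs do not capture this.
- The Introduction describes a population-based study on real-world data with no decision model. Cost and stroke are observed in the same patients, so their joint uncertainty can be computed directly.

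The results are meant for decision-makers and evaluating bodies. They could be told that the cost per stroke avoided is robust when the data do not exclude zero benefit.

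**Working it through.** The article gives no stroke rate, effect size, cost difference, standard deviation or expected ratio. There is no figure of its own to reproduce, and what follows is illustration.

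**Input from the article.** Group sizes of 41,430 (VKA) and 19,548 (DOAC), section 2.2. These are 2017 registry counts of treated patients, before any loss to the eligibility criteria.

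**Assumed inputs.** VKA 2-year stroke risk pV; risk ratio RR, so that pD = RR × pV; incremental cost ΔC; two-sided 95% intervals. ΔC is held fixed so that only sampling error in the denominator is shown.

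**Formulas.**
- Strokes avoided: d = pV − pD
- SE(d) = √[pV(1 − pV)/41,430 + pD(1 − pD)/19,548]
- Ratio = ΔC/d; its range comes from dividing ΔC by d ± 1.96 × SE(d)

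**Case A: pV = 2.50%, RR = 0.90, so pD = 2.25%; ΔC = EUR 1,500.**
- d = 0.0025
- SE = √(0.025 × 0.975/41,430 + 0.0225 × 0.9775/19,548) = 0.00131
- 95% CI for d: −0.00007 to 0.00507, that is −0.01 to 0.51 percentage points
- Ratio = 1,500/0.0025 = EUR 600,000. The favourable limit is 1,500/0.00507, about EUR 296,000. The other limit of d is below zero, so no stroke is avoided and the ratio has no upper bound.

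**Case B: pV = 2.50%, RR = 0.80, so pD = 2.00%; ΔC = EUR 1,500.**
- d = 0.0050, SE = 0.00126, 95% CI 0.00253 to 0.00747
- Ratio = EUR 300,000, range about EUR 201,000 to 593,000

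**Wider range of assumptions (pV 1% to 4%, RR 0.80 to 0.95).** The relative standard error of d, SE(d)/d, runs from 20% (pV 4%, RR 0.80) to 170% (pV 1%, RR 0.95). At pV 2% and RR 0.90, power to detect the stroke difference is 38.5%. At pV 4% and RR 0.80 it is 99.9%.

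**Sampling error in the numerator, for comparison.** SE(ΔC) = SD × √(1/41,430 + 1/19,548). For an assumed SD of EUR 5,000 to 15,000 this is EUR 43 to 130. Relative to ΔC:

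| Assumed ΔC (EUR) | Relative SE of ΔC |
|---|---|
| 1,500 | 3% to 9% |
| 1,000 | 4% to 13% |
| 500 | 9% to 26% |
| 200 | 22% to 65% |

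For ΔC of about EUR 1,000 or more, the denominator is the noisier part throughout the range examined. For a small ΔC and a large stroke effect the order can reverse, for example 65% against 20%.

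**The case against.** The strongest reply is that this is a condensed article. It says that a one-way analysis will be done and does not exclude others. It also commits to published methodological guidance for economic evaluation, and an interval method for the ratio could sit in a fuller plan. This stands to a degree: the absence of a joint interval is partly inferred from silence. But the article does more than stay silent. It names the method in both the abstract and section 2.8, limits it to cost items and prices, and assigns it the task of testing robustness. That stated match of method to purpose is unsuitable whatever else may be planned.

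The second reply is that the figures rest on assumed risks and costs. That is correct. In Case B the interval stays clear of zero, so an undefined or negative ratio is one scenario among several.

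A reader might also infer three stronger claims that the article does not support.

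- *That sampling error in strokes avoided is the largest source of uncertainty.* No stated input allows a ranking. Error in cost can exceed it, and confounding between non-randomised groups could exceed both.
- *That price variation would always look tight beside it.* The incremental cost is a net of several components. With an assumed DOAC drug cost of EUR 2,000 and a net increment of EUR 500, a 20% price change is EUR 400, or 80% of the increment.
- *That clustering within the 287 primary care centres must widen the interval.* Both drug groups can occur in the same centre, so shared centre effects may partly cancel. No intracluster figure is given.

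**Conclusion.** The concern holds as a mismatch between a stated method and its stated role. Varying cost items one at a time can show sensitivity to prices. It cannot show that the cost per stroke avoided is robust, because the denominator and its link to cost are left untouched. Sampling error is not ignored altogether, since intervals for mean costs are planned, but as described it does not reach the ratio.

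The gap is likely to be material. Even with some 61,000 patients, a risk ratio of 0.90 from an assumed 2.50% baseline leaves the ratio without an upper bound, and a risk ratio of 0.80 leaves roughly a threefold range (593,000/201,000 ≈ 3.0). These sizes depend on the assumed risks, on the assumed EUR 1,500, and on the registry counts surviving eligibility. The mismatch itself does not depend on them. This should be changed before analysis.

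**What to change.** Add to section 2.8 a non-parametric bootstrap of patients that draws each patient's cost and stroke outcome together, and repeats within each replicate any adjustment used for the comparison. From the replicates, report the cost-effectiveness plane and either the incremental net benefit with its 95% confidence interval or an acceptability curve, over a stated range of values per stroke avoided. The article sets no such value, so a range is needed.

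Keep the one-way analysis for unit prices, and reword its purpose so that the robustness claim covers price uncertainty only. Align the abstract.

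No new data are needed. The cost is a few sentences of plan text, some computing time, and a headline result that will look less precise.

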## Ethics and dissemination

3

This study will be carried out in accordance with the norms and principles of the Declaration of Helsinki. The protocol was approved by the Clinical Research Ethics Committee of the *Fundació Institut Universitari per a la recerca a l’ Atenció Primària de salut Jordi Gol i Gurina (IDIAPJGol)* on May 30, 2018 with code P18/080, and has also been authorized by the Primary Healthcare Directorate of the ICS. The SIDIAP database provides anonymised data, identified with an internal code, which makes it impossible, even for the research team, to identify any subject. For the same reason, informed consent will not be obtained. By these means, the confidentiality of the data of the individuals included in the study will be guaranteed, in accordance with the Organic Law on Protection of Personal Data (03/2018 of December 5, and in accordance with the provisions of the Regulation 2016/679 of the European Parliament and of the Council of 27 April 2016 on data protection, and all applicable national regulations. If any modification is required, it will be presented to the IDIAPJGol Clinical Research Ethics Committee for approval.

The results and conclusions of this study will be disseminated in Spain, as well as in international scientific and professional forums, with the results published in indexed scientific journals.

## Discussion

4

The aim of the present study is to carry out an economic evaluation of all the anticoagulants indicated for the prevention of thromboembolic complications in patients with NVAF.

VKAs are the most used anticoagulants worldwide.^[40]^ However, the administration criteria differs in each country. For example, while in Continental Europe, the VKA most widely used is the acenocoumarol, in the United States and the rest of Europe, it is the warfarin.^[41]^ Several studies have been carried out with warfarin. ^[15,16,19,20,25,42]^ Though, there is scarce literature on acenocoumarol, ^[21,22,24,27]^ which is the most popular VKA in Spain. In the clinical practice, the results of the studies including warfarin are assumed to be generalizable.^[7]^ Nevertheless, and from the best of our knowledge, there is no evidence to support this assumption.

The main strength of our study is the analysis of all marketed anticoagulants from Spain, which will provide strong evidence about their differences, including both VKAs (warfarin and acenocoumarol). Another strength includes the quantification of indirect costs, such as the loss of productivity, associated with the 2 types of treatments. Since it is a population-based study, with RWD, more accurate and representative information will be available for health decision-makers.^[43,44]^ Moreover, most of the published research on this topic is based on hospital data, whereas our project will include variables and expenses related to PC settings, where most VKA controls are performed in our milieu.

### Limitations

4.1

Our study has certain limitations. First, the database includes data that are dependent on the professional registry, which means that there may be some under-registration of some variables of interest. In addition, there are expenses that we cannot determine, such as those of medical transport or the journeys undertaken by patients themselves, which could therefore lead to the costs of VKA being underestimated. Also, we will not be able to include intangible costs (as patient suffering due to complications or caregiver overload) and operating costs, (such as overheads: water, furniture, building maintenance and input costs). However, these limitations should affect both groups of anticoagulants equally, so it is reasonable to assume that they will not have a significant impact on the result. Finally, a time horizon of 2 years could be too short a time for a health event to occur.

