## Introduction

1

Atrial fibrillation (AF) is the most common arrhythmia in western countries and is associated with high morbidity and mortality, thereby constituting a major public health problem.^[1,2]^ It is 1 of the most frequent causes of ischaemic stroke.^[3,4]^ Anticoagulant therapy is used for stroke prevention, for which there are 2 main groups of drugs —vitamin K antagonists (VKAs) and direct-acting oral anticoagulants (DOACs)— which have both proved effective and safe in the long term.^[5]^

VKAs have been widely used for a long time and their efficacy in preventing strokes and systemic embolism in patients with nonvalvular atrial fibrillation (NVAF) is well established.^[6]^ However, most of the studies have involved warfarin, and the results have been generalized to all VKAs.^[7]^ The price of these drugs is low (compared with that of DOACs),^[8]^ although they generate direct and indirect costs. Furthermore, they have limitations such as interindividual and intraindividual variability of response, a slow onset of action, a narrow therapeutic margin, a need for dose-adjustment through periodic controls of the international normalized ratio, and interactions with some foods and medications.^[9–11]^

In recent years, DOACs have emerged that have more predictable anticoagulant effects and fewer interactions with other drugs, and that allow a fixed dosage regimen, without the need for monitoring.^[12]^ Overall, DOACs present a favorable risk prevention profile, with significantly lower levels of strokes, intracranial haemorrhages and mortality compared with VKAs, but they have a higher risk of gastrointestinal bleeding^[7]^ and are expensive.^[8]^ It is also important to take into account the adjustment of the dosage according to age, weight, and renal function, in addition to monitoring compliance, because highly variable therapeutic adherence rates have been noted.^[7,13]^

The European and American guidelines recommend the use of any DOACs rather than VKAs because of their net clinical benefit, except in selected cases.^[14–16]^ However, the use of DOACs in clinical practice is determined by the recommendations of the health authorities of each country. In Spain, VKAs are recommended as the first choice, with DOACs being used when specifically recommended,^[17]^ although currently it has been observed that more than 80% of physicians are starting treatments with DOACs .^[18]^

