### Data source

2.3

At ICS, more than 9175 professionals working in PC use the same computerized medical history program, called eCAP. eCAP data will be obtained through SIDIAP, which is a unique database, previously validated, and highly representative of the Catalan population.^[29,30]^

In this way, SIDIAP provides, from each of the 5.8 million citizens assigned to the various PCCs of the ICS, information linked to a unique, anonymised identifier. The following information will be obtained from all NVAF patients receiving anticoagulants on January 1, 2017:

(1)data from the eCAP program: demographic data, PC visits, health events, clinical variables, referrals, deaths, prescriptions and sick leave;(2)laboratory results: these will be extracted directly from the laboratory database, rather than depending on manual records, thereby guaranteeing data quality;(3)medication dispensed by pharmacy offices: this information will be obtained directly from those offices;(4)other, external sources of information: (4.1.) *Conjunt Minim Bàsic de Dades* (CMBD), which is a population registry that collects ICD-9 pathology data linked to hospitalization at all of the Hospitals in Catalonia,^[31]^ (4.2.) Mortality: data supplied by the Department of Health, including cause and date of all deaths of residents of Catalonia.^[28]^

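### Section 4.1 assumes that under-registration affects both groups equally, but events recorded only in primary care may be captured more completely under VKA, which would favour DOACs.

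*Protocol article*

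**What the plan says.** **Registration.** Section 4.1 (Limitations) states that "the database includes data that are dependent on the professional registry, which means that there may be some under-registration of some variables of interest". After adding several uncounted costs, the paragraph concludes that its limitations bear equally on the two drug groups and should not materially change the result. It offers no evidence for this.

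**Sources.** Section 2.3 (Data source) lists "data from the eCAP program: demographic data, PC visits, health events, clinical variables, referrals, deaths, prescriptions and sick leave". The same list includes the hospital registry CMBD, "which is a population registry that collects ICD-9 pathology data linked to hospitalization at all of the Hospitals in Catalonia", and mortality data, "data supplied by the Department of Health, including cause and date of all deaths of residents of Catalonia". Table 1, which gives the source of each variable, is not shown in the text available.

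**Contact with primary care.** The Introduction says that VKAs carry "a need for dose-adjustment through periodic controls of the international normalized ratio" and that DOACs can be given "without the need for monitoring". The Discussion (section 4) describes primary care as the setting "where most VKA controls are performed in our milieu".

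**Use of the events.** Section 2.6 bases the cost-effectiveness indicator on the number of ischaemic strokes registered in each group over the two years. TIA, angina, intracranial and gastrointestinal haemorrhage and other haemorrhages are among the secondary events.

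**The concern.** The equality statement is a positive claim about validity. It does not follow from the rest of the protocol. If one group is seen in primary care on a schedule because of its drug and the other is not, the first group has more occasions for an event to be entered in the primary care record. This is ordinary surveillance bias, and each element of the mechanism is in the protocol.

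The stake is the main result. Cost per stroke avoided divides a cost difference by a difference between two stroke rates. Incomplete registration that is worse under DOAC lowers the DOAC rate and so creates avoided strokes that did not occur. Adjusting for patient characteristics does not remove this, because the error lies in the outcome. Secondary events that often do not lead to admission, such as TIA and minor bleeding, are the most exposed.

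**Working it through.** The protocol gives no stroke rate, no completeness of registration and no visit counts, so there is no stated figure to reproduce. The check has two parts.

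**1. The sections side by side.**

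- Section 4.1: some professionally entered variables may be under-registered, and the effect is taken to be equal by group.
- Section 2.3: health events are among the data entered in eCAP.
- Introduction and Discussion: VKA treatment brings periodic INR controls, mostly in primary care. DOAC treatment does not bring these controls.

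Together these give a reason why registration in eCAP may differ by group. They do not show that it does. Section 2.3 also names two sources that do not depend on primary care visits, so the exposure is confined to events that appear in eCAP alone.

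**2. An illustration of size.**

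Assumptions, none of them in the documents:

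- The true two-year stroke risk *p* is the same in both groups: 1%, 2% or 4%.
- *h* is the share of strokes found in hospital or death data whatever the primary care contact, and is the same in both groups.
- *s* is the share of the remaining strokes that eCAP captures: 95% under VKA, and 90% or 80% under DOAC.

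Formulas:

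- Capture in a group: *c* = *h* + (1 − *h*) × *s*
- Observed DOAC/VKA rate ratio: *c*(DOAC) / *c*(VKA)
- Falsely avoided strokes per 1,000: 1,000 × *p* × [*c*(VKA) − *c*(DOAC)]

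Example with *h* = 0.5 and DOAC capture 80%: *c*(VKA) = 0.5 + 0.5 × 0.95 = 0.975 and *c*(DOAC) = 0.5 + 0.5 × 0.80 = 0.90. The ratio is 0.90 / 0.975 = 0.923. At *p* = 2% the false difference is 1,000 × 0.02 × 0.075 = 1.5 per 1,000.

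| *h* | *c*(VKA) | *c*(DOAC), *s* = 90% / 80% | False rate ratio | Falsely avoided per 1,000, *p* = 1% to 4% |
|---|---|---|---|---|
| 0 | 0.95 | 0.90 / 0.80 | 0.947 / 0.842 | 0.5–2.0 / 1.5–6.0 |
| 0.5 | 0.975 | 0.95 / 0.90 | 0.974 / 0.923 | 0.25–1.0 / 0.75–3.0 |
| 0.8 | 0.99 | 0.98 / 0.96 | 0.990 / 0.970 | 0.1–0.4 / 0.3–1.2 |
| 1 | 1 | 1 / 1 | 1 / 1 | 0 / 0 |

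Section 2.2 gives 41,430 VKA and 19,548 DOAC patients. With these numbers, the chance of a nominally significant difference in favour of DOACs (two-sided 5% test, so 2.5% with no bias) is 8–96% at *h* = 0, 5–44% at *h* = 0.5 and 3–10% at *h* = 0.8, across the same values of *p* and *s*.

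**The case against.** The strongest reply is that eCAP is only one of the linked sources. CMBD covers every hospital in Catalonia and the mortality data cover all deaths with cause. Nothing says that strokes are counted from eCAP alone, and Table 1 may already name CMBD for stroke. An ischaemic stroke is also serious enough that most may be found through admission or death. This stands. It means that the missing source rule cannot be charged against the plan, and it limits the likely size for the primary event.

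A reader might go further and infer that the study's health events simply come from primary care records, or that registration does differ by group. The documents support neither. Section 2.3 contradicts the first. The second would need completeness or visit figures by group, and none is given. The Introduction also mentions dose adjustment and monitoring of compliance for DOACs, so their patients are not described as free of follow-up. Nor does it help to argue that a patient who dies in hospital never returns to have the stroke entered: that applies to either drug, and the mortality data would record the death and its cause.

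Section 4.1 speaks only of some variables and does not name health events. Even so, section 2.3 places health events among the eCAP data, and the equality statement exempts nothing. That statement remains unsupported for event registration whichever source defines stroke, and it extends to the secondary events.

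**Conclusion.** The concern holds in a limited form. The claim that under-registration is equal in the two groups is unsupported, and the protocol's own description of care gives a reason why it may be wrong for events recorded only in eCAP. If so, the bias in avoided strokes would favour DOACs.

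The size cannot be determined from the documents. Under the assumed capture rates, the false rate ratio runs from 0.84 with no capture outside primary care, through 0.97–0.99 with 80% captured elsewhere, to no bias with full capture. The direction rests on VKA patients having more primary care contact, which is inferred from the text and not measured. The size rests on how far CMBD and mortality data are used to find events. The point should be dealt with before analysis, but it does not show that the primary comparison is biased.

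**What to change.** - **Section 4.1:** withdraw the equal-effect statement for event registration. Say instead that events recorded only in eCAP may be captured more completely under VKA.
- **Section 2.6:** state that ischaemic stroke is ascertained in both groups from CMBD diagnoses and mortality-registry cause of death as well as eCAP. If Table 1 already says so, a cross-reference is enough.
- **Results:** report by group the share of events found only in eCAP.
- **Sensitivity analysis (2.8):** repeat the avoided-strokes and cost-per-stroke-avoided analysis restricted to strokes in CMBD or the mortality registry. Do the same for intracranial and hospitalised gastrointestinal haemorrhage.

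Making registry-captured strokes the only primary definition is a possible alternative. It is debatable, because it removes non-admitted strokes from the main count and the documents do not say how many there are.

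The cost is a little more analysis, with no new data, since both registries are among the listed sources. The restricted analysis omits non-admitted strokes, which is why it should stand beside the full count and not replace it.

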### Cost estimation

2.5

Cost estimates will take into account direct expenses (from pharmacy, PC, emergencies and hospitalisation) and indirect expenses (loss of productivity), from a social perspective, in patients diagnosed with NVAF and treatment with oral anticoagulants. Two groups will be established: patients receiving VKAs and those receiving DOACs. We will use a 3% discount rate, which will be applied in the second year.

We will use the charges set out in the *Diari Oficial de la Generalitat de Catalunya* (DOGC)^[32]^ closest to the date of analysis (2014) to estimate the costs. The euro will be used as the reference currency (which will not require conversion). Prices will be adjusted to those of 2018 to take into account inflation in the health sector.^[33]^ The costs of hospital admissions will be obtained from the *Grups Relacionats amb el Diagnòstic* (GRD) patient classification system, published in the DOGC.^[34,35]^ For drug prices, the retail price taken from pharmacy billing data will be used. The final costs of the 2 study groups (patients treated with VKAs and those treated with DOACs) will be calculated by quantifying the resources consumed by each individual with respect to each variable and then multiplying by the cost of each resource. This procedure will yield the total cost of the resource per individual, as well as the total cost for each study group.

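### Section 4.1 says omitted travel could understate VKA cost, then that the omissions affect both groups equally; for travel the protocol's own facts point to a bias against DOACs that no named analysis addresses

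*Protocol article*

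**What the plan says.** Four parts of the protocol article bear on this point.

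- **Section 4.1, Limitations.** The authors write that "there are expenses that we cannot determine, such as those of medical transport or the journeys undertaken by patients themselves", and give the consequence for one group only: "which could therefore lead to the costs of VKA being underestimated". The next sentence adds two further kinds of omission, intangible costs and operating costs. Then comes the conclusion: "However, these limitations should affect both groups of anticoagulants equally, so it is reasonable to assume that they will not have a significant impact".
- **Introduction and Discussion.** Among the drawbacks of VKAs the Introduction lists "a need for dose-adjustment through periodic controls of the international normalized ratio". DOACs, by contrast, "allow a fixed dosage regimen, without the need for monitoring". The Discussion describes primary care as the setting "where most VKA controls are performed in our milieu".
- **Sections 2.5 and 2.6.** Costs are counted "from a social perspective, in patients diagnosed with NVAF and treatment with oral anticoagulants". The components are pharmacy, primary care, emergency, hospital and lost productivity; travel is not among them. The main indicator sets the cost of the two groups against the strokes recorded in each, to give the cost of avoiding one stroke.
- **Section 2.8, Sensitivity analysis.** The only sensitivity analysis described is one-way and deterministic, "in the items which the greatest impact on the composition of the cost, or in which there may be a uncertainty with the real price". Travel is not named.

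**The concern.** An omission that is the same in both groups drops out of a cost difference; one that falls mainly on one group does not. Section 4.1 first describes travel as the second kind and then treats all the omissions as the first kind. If the second statement is carried into the interpretation, readers will be told that the missing costs do not matter, although the protocol's own account of the two drug classes suggests they lean one way.

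At stake is the numerator of the main result. If VKA cost is understated, DOACs look more expensive relative to VKAs than they are. The quotient is sensitive to this because a per-patient cost difference is divided by a difference in stroke risk, which is likely to be small over two years. The declared social perspective adds weight, since patients' travel is relevant to it, and section 4.2 hopes the results will inform evaluating bodies.

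**Working it through.** The document gives no figure for the omitted cost, so there is nothing to reproduce. The check is first textual; the arithmetic after it only illustrates scale.

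**1. The statements side by side**

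| Place | Effect of the omission |
|---|---|
| 4.1, on transport and journeys | VKA cost could be too low; nothing corresponding is said for DOACs |
| 4.1, closing statement on these limitations | Equal in both groups, so no significant impact |
| Introduction | Periodic INR controls for VKAs; no monitoring need for DOACs |
| Discussion | Most VKA controls take place in primary care |

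Controls required by one class and not by the other generate journeys mainly in one group. The Introduction and the Discussion therefore support the first statement and not the second, as far as travel is concerned.

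**2. Direction**

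Let T_V and T_D be the uncounted travel cost per patient on VKA and on DOAC.

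- True cost difference = (C_D + T_D) − (C_V + T_V)
- Measured cost difference = C_D − C_V
- Measured minus true = T_V − T_D

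This is zero only if travel is equal in the two groups. If T_V exceeds T_D, the measured difference is too large and the error goes against DOACs.

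**3. Scale, for illustration only**

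Inputs from the document: two-year horizon (section 2.1) and 3% discount applied in the second year (section 2.5).

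Inputs assumed, not in the document: 6 to 18 more visits a year on VKA than on DOAC; EUR 2 to 10 of travel per visit; DOACs avoid strokes, with an absolute two-year risk difference of 0.25 to 1.0 percentage points. The patient is taken to be followed for the full two years.

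- Discount factor = 1 + 1/1.03 = 1.971
- Omitted net cost per VKA patient = extra visits per year × cost per visit × 1.971
- Shift in cost per avoided stroke = omitted cost ÷ risk difference

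| Extra visits/year | EUR/visit | Omitted per patient | Shift at 1.0 point | at 0.5 point | at 0.25 point |
|---|---|---|---|---|---|
| 6 | 2 | EUR 24 | EUR 2,365 | EUR 4,730 | EUR 9,460 |
| 12 | 5 | EUR 118 | EUR 11,825 | EUR 23,650 | EUR 47,301 |
| 18 | 10 | EUR 355 | EUR 35,476 | EUR 70,951 | EUR 141,903 |

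The range runs from about EUR 2,400 to EUR 142,000 per avoided stroke. A span that wide is no estimate. It shows that a modest sum per patient need not be negligible once it is divided by a small risk difference.

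**The case against.** The best defence is that the closing statement may refer only to the sentence directly before it, on intangible and operating costs. Equality is plausible for overheads, and the contradiction would then disappear. The wording does not restrict it that way, and the plural most naturally covers the whole list of omissions. On the narrow reading the admitted travel bias is left without any response, so section 4.1 needs a correction either way.

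Several stronger readings are tempting, and the objections to them stand:

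- **That the bias is known or certain.** Section 4.1 says only that it could arise. Some omitted travel is unrelated to INR controls: medical transport is also listed, and the Introduction mentions dose adjustment by renal function and compliance monitoring for DOACs. What matters is the net difference.
- **That the omission is never tested.** A journal article condenses the full protocol, and the full list of scenarios may be elsewhere. The uncertain-price clause in section 2.8 could be stretched to cover travel. All that can be said is that no analysis named here addresses it.
- **That the result is overstated by a given percentage.** The article supplies no visit frequency, unit travel cost or expected cost difference, so any percentage would be a ratio of assumptions.
- **That patient and companion time is also missing.** The article does not say so. Lost productivity is counted under section 2.5, and adding time to travel could count it twice.
- **That the perspective is mislabelled.** The components are listed and the omissions disclosed; a different label is a matter of preference.

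It is also fair to say that the authors have already stated a direction in part, and that no endpoint or specified analysis is shown to be wrong.

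**Conclusion.** The point holds in a limited form. For travel costs, the assurance of equal effect in section 4.1 conflicts with the sentence on VKA cost in the same paragraph and with the protocol's description of monitoring. The omission would tend to bias the cost per avoided stroke against DOACs, and nothing named in this document examines it. The direction rests on VKA patients making more uncounted journeys than DOAC patients on balance, which the Introduction and the Discussion support but do not measure. The size is unknown: the illustrative figures depend wholly on assumed visits, unit costs and risk differences. They do not show that the bias is large, but the article gives equally little ground for calling it insignificant.

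**What to change.** 1. In section 4.1, confine the equality statement to the overhead items, and say separately that leaving out transport and journeys is likely to understate VKA cost and so bias the comparison against DOACs.
2. In section 2.8, add one pre-stated one-way scenario: VKA control visits multiplied by a low, base and high travel cost per visit, with DOAC visits costed by the same rule so that only the net difference enters. A threshold version serves equally well: report the travel cost per visit at which the conclusion would change.
3. Take visit counts from the primary care visits already extracted under section 2.3, if control visits can be told apart from other visits. The article does not show that they can, and it says that most, not all, controls take place in primary care. If they cannot be separated, use an assumed range.

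The cost is a text correction and one added scenario, with no new data collection. The drawback is that the unit travel cost, and possibly the visit count, would be an assumption and must be shown as a range.
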